**Project site**

The project will be implemented in rural parts of Lilongwe district. Ideally, the study region would be divided into “clusters”, each consisting of geographically delineated area (defined by a combination of at least 2 traditional authorities). The clusters would then be randomised to either receive the intervention (Early intervention arm) or to act as a control, (Delayed intervention arm) using stratification methods to ensure that the two sets of clusters would be as similar as possible in terms of their poverty profile, population structure, health service coverage, and presence of significant number of at least one of the selected community-based health care providers (store-keepers, ante-natal care clinic and home-based care organisations).

The problem with this methodology is that people in the study clusters do not always attend their “local” health centre, so there would be considerable problems of “pollution” between the two study groups, in that people living in intervention clusters would attend control cluster health centres, and vice versa. While it would be technically relatively simple to identify the location of participants’ homes (and hence do an “intention-to-treat” analysis with individuals assessed according to their actual residence address rather than health centre attended), this would not eliminate the likelihood that some people resident in control clusters would be exposed to the intervention and some people resident in intervention clusters would not be exposed to it. The decision was thus taken to divide the rural parts of Lilongwe district into just six groups with large population sizes of at least 166,000. A random number will be generated in Excel to determine which clusters will receive the intervention early and which will ones will receive the intervention later. Thus, the six study clusters will equally be randomised to the Early intervention arm (to receive the intervention early in the first 12 months) and the Delayed intervention arm (to receive the intervention after 12 months). The 6 clusters will be pair-matched according to population sizes and their proximity to the urban areas.

Because the intervention is to be implemented at community level, allocation of the intervention will not be blinded to the communities and the research team implementing the intervention. However, allocation of TB and HIV cases to the clusters will be blinded.

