**Data collection process**

*Sample size*

Qualitative research

The actual sample size for the qualitative element of the study is unknown at the outset**.** The sample size will be determined when the “point of saturation” is reached (this is the point at which no new information emerges from each group of respondents). However, indicative figures for the qualitative component are 10 – 20 key informants, 20 semi-structured interviews, and 20 in-depth interviews and twenty-four focus group discussions (six for each respondent category).

Quantitative research

The sample size for the quantitative element of this study needs to provide sufficient power to detect clinically important effect sizes for both TB and HIV. The statistical analysis will thus involve multiple comparisons. The exact number of comparisons of primary interest will be kept to a minimum – but to ensure multiple comparison issues are accounted for, all of the sample size / power calculations detailed below are based on an alpha level of 1% rather than the conventional 5% level.

- - - - 1. TB

*Primary outcome measure*: number of TB patients starting treatment - the expected proportion of smear positive cases starting treatment in the control group is estimated to be 55% - an increase in this proportion to 70% in the intervention group will be considered clinically significant.

WHO estimates that Malawi is detecting less than 50% of smear-positive TB cases nation-wide (the international case detection target is 70%). Based on secondary data collected to date:

- the current catchment population of the Lilongwe District rural health centres in the two study clusters is approximately 1.1 million
- the total number of TB cases registered in these rural health centres for which data is available was 936, of which 329 were smear positives and the remaining 607 were smear negative and other forms of TB.

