Thus, assuming that actual TB cases are not rising in the community year on year, the expected number of smear positive TB cases registering for treatment in each study group over a one year period would be (329 / 2 =) 165, with at least as many smear negatives and other forms of TB. As this constitutes 55% of all smear positive TB cases, the actual number of smear positive TB cases occurring in each study group will be (165 / 0.55 =) 300. This will provide 87.5% power to detect an increase in the number of smear positive TB cases registering for treatment from 165 (55%) in the control group to 210 (70%) in the intervention group. Given that 41% of the TB cases were smear positive (WHO, 2009), then 512 TB cases (all forms of TB) were expected to start TB treatment at the end of the intervention in the intervention arm.

- - - - 1. HIV

*Primary outcome measure*: number of HIV-infected patients starting ART – the expected proportion of HIV-infected patients starting ART in this region of Malawi is currently estimated to be 15% - an increase in this proportion to 18% (a 20% proportional increase) in the intervention group would be considered clinically significant.

The population of Malawi is approximately 11 million, of which (approximately) 1.1 million (10%) live in the rural areas of Lilongwe. Estimates taken from Malawi’s 5 year ART Scale-Up plan indicate that 85,000 new patients become eligible for ART each year across the country, so 8,500 new patients become eligible for ART in the rural areas of Lilongwe. Data collected by the REACH Trust indicate that the ART programme starts 1,300 people on treatment in the Lilongwe rural health facilities per year, a treatment initiation rate of (1300 / 8500 =) 15%. Thus, the number of new patients becoming eligible for ART in each of the two study groups will be 4,250. This will provide 86.9% power to detect a 20% increase in the proportion of eligible patients starting ART (in absolute terms, from 15% in the control group to 18% in the intervention group).

It is hoped that the intervention will have a much greater impact on the primary outcome measure, increasing the proportion of eligible patients starting ART in the intervention group well towards the national target figure of 50%.

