Qualitative data will be transcribed verbatim. The transcribed data will be saved as rich text file (RTF) format which will be imported in MAXQDA. It will be organised according to themes for analysis.

The quantitative data will be collected and stored using pre-prepared Excel, Access and/or EpiInfo software databases. The characteristic of the control and intervention groups will initially be summarised and compared using standard univariate statistical methods (Fisher exact test and Student t-test/Mann-Whitney U-tests for categorical and continuous measures respectively). Effect sizes for the primary and main secondary measures will be summarised using incidence rate ratios with their 95% confidence intervals. Poisson regression methods will be used to investigate in greater detail the factors influencing the two primary outcome measures, and to adjust the effect estimates for confounding factors. The analyses will be conducted using the SPSS and Stata statistical packages at the REACH Trust, with supervision and advice as necessary provided by [name] (Senior Lecturer in Medical Statistics, Liverpool School of Tropical Medicine).

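### Both primary outcomes are to be analysed by rate ratios and Poisson regression with no stated allowance for the six randomised clusters, so as written the intervals are too narrow by an amount that depends on unknown between-cluster variation

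*Protocol*

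**What the plan says.** Design (Protocol, Project site): "the six study clusters will equally be randomised to the Early intervention arm" or to a delayed arm, and "The 6 clusters will be pair-matched according to population sizes and their proximity to the urban areas". That gives three clusters per arm in three pairs.

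Analysis (Protocol, Data analysis, under Data collection process): effects on the primary and main secondary measures are to be given as "incidence rate ratios with their 95% confidence intervals". For modelling, "Poisson regression methods will be used to investigate in greater detail the factors influencing the two primary outcome measures", and the same models are to adjust for confounding. The section mentions no cluster term, random effect, robust or overdispersed variance, pair term or small-sample correction.

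The univariate tests have a separate role: "The characteristic of the control and intervention groups will initially be summarised and compared using standard univariate statistical methods".

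Sample size (same part of the protocol): the calculations are "based on an alpha level of 1% rather than the conventional 5% level". The section ends by recognising the move to six large clusters and promising a simulation-based sample size calculation, to be done before the analysis and to guide the analysis plan. It gives no intracluster correlation or between-cluster coefficient of variation.

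**The concern.** The cluster is the unit of randomisation, but the stated analysis follows the count of patients. A Poisson interval without a cluster term treats each treatment start as independent and reflects only counting error. Differences between areas in wealth, access and services, which the Project site section itself treats as needing balance, are left out of the standard error. With three clusters per arm they do not average out, so an ordinary difference between areas can be reported as an intervention effect. The problem grows with the count per cluster, so ART is hit harder than TB. Both primary outcomes are affected, and the findings are meant to inform national policy and replication.

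**Working it through.** **1. The plan's own power figures.** Inputs are from Sample size, Quantitative research. For TB, "the actual number of smear positive TB cases occurring in each study group will be (165 / 0.55 =) 300", with 55% v 70% starting treatment. For ART, 4,250 per group with 15% v 18%. Alpha is 1%, taken as two-sided (z=2.576).

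Power = Φ[(d − 1/n − z·s0)/s1], where s0 is the pooled SE, s1 the unpooled SE and 1/n the continuity correction.
- TB: s0 = √(2×0.625×0.375/300) = 0.03953 and s1 = 0.03905. Without the correction (0.15 − 0.1018)/0.03905 = 1.234, giving 89.1%. With it, 1.148, giving 87.5%.
- ART: s0 = 0.008052 and s1 = 0.008045. Without the correction 1.151, giving 87.5%. With it, 1.122, giving 86.9%.

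The stated 87.5% and 86.9% are reproduced exactly by a two-proportion calculation for independent patients (design effect 1).

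**2. True error of a Poisson test with no cluster term.** Expected starts per arm with no effect are 165 (TB) and 1,300/2 = 650 (ART), so the mean per cluster is m = 55 and 216.7. The between-cluster coefficient of variation k is an assumption. So is the share s of between-cluster variance that the pairs absorb.

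Variance inflation = 1 + m·k²·(1 − s). True error ≈ 2[1 − Φ(1.96/√inflation)].

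Examples at k=0.10, s=0:
- TB: 1 + 55×0.01 = 1.55; √ = 1.245; 1.96/1.245 = 1.574; error 11.5%.
- ART: 1 + 216.7×0.01 = 3.167; √ = 1.780; 1.96/1.780 = 1.101; error 27.1%.

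Simulation (200,000 null trials per setting, lognormal cluster rates, 3 v 3) agrees to within about one percentage point. Simulated true error at nominal 5%:

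| k (assumed) | TB, s=0 | TB, s=0.5 | TB, s=0.9 | ART, s=0 | ART, s=0.5 | ART, s=0.9 |
|---|---|---|---|---|---|---|
| 0.05 | 6.6% | 5.7% | 5.1% | 11.4% | 8.2% | 5.6% |
| 0.10 | 11.5% | 8.1% | 5.7% | 27.0% | 17.4% | 7.5% |
| 0.20 | 27.0% | 17.4% | 7.4% | 52.5% | 39.4% | 15.1% |
| 0.30 | 41.4% | 29.1% | 10.7% | 66.0% | 54.7% | 25.3% |

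At k=0 the error is nominal. Testing at 1% does not remove the problem: with s=0 and k=0.10 the true error at nominal 1% is 3.8% (TB) and 14.6% (ART).

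**3. Cluster-level comparison in the same simulations.** A paired t-test on log counts (2 df) held about 5% throughout. An unpaired t-test (4 df) held about 5% when matching was ineffective. It was conservative when matching worked: for TB with s=0.5 and k=0.1–0.3, its error was 3.7% down to 2.5%.

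**4. Power of a cluster-level t-test for the stated effects** (165 v 210 TB starts; 15% v 18% of 4,250 for ART; matching ineffective):

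| k (assumed) | TB paired / unpaired, 5% | TB, 1% | ART paired / unpaired, 5% | ART, 1% |
|---|---|---|---|---|
| 0 | 27% / 43% | 6% / 14% | 46% / 72% | 12% / 32% |
| 0.10 | 19% / 29% | 4% / 8% | 20% / 30% | 4% / 9% |
| 0.30 | 9% / 11% | 2% / 3% | 8% / 9% | 1.5% / 2% |

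Effective matching moves the paired figures up towards the k=0 row, not beyond it.

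**5. Randomisation floor.** Three pairs allow 2³ = 8 allocations, so the smallest two-sided exact p is 2/8 = 0.25. Without pairing there are C(6,3) = 20 allocations, and the floor is 2/20 = 0.10. Neither needs an assumed k.

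**The case against.** The strongest reply is that this argues from silence. An analysis plan may exist, the protocol says simulations will guide it, and Poisson regression can be fitted with robust or random cluster effects. Part of that stands: the protocol does not rule out a cluster-adjusted model. But it does fix the effect measure, the interval and the model, and the promised simulations concern sample size and carry no commitment on method. As written, the text leads to unadjusted intervals.

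Four stronger readings are tempting, and the protocol does not support them.
- **That the false-positive rate is several times nominal as a fact.** The protocol gives no between-cluster variation. For TB at k=0.05, or with highly effective pairs at modest k, the inflation is small. An analysis using the planned baseline measurements would also depend on variation in change between clusters, which is not modelled here.
- **That the univariate tests inflate the primary error.** The "Fisher exact test and Student t-test/Mann-Whitney U-tests for categorical and continuous measures respectively" are named only for an initial comparison of group characteristics, not for the effect.
- **That ignoring the pairs narrows the intervals.** It does not. The narrowing comes from ignoring clusters; leaving effective pairs out of a cluster-level test costs precision and makes it conservative.
- **That several cluster-level covariates are planned.** The protocol speaks of confounders without number or level. Six clusters would still support very few.

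**Conclusion.** The point holds as a defect in the written analysis: six pair-matched clusters are randomised, and the method named for both primary outcomes makes no allowance for clustering. The intervals are too narrow if rates vary between clusters within pairs.

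The size is conditional. Over assumed k of 0.1 to 0.3, true error at nominal 5% is about 12–41% (TB) and 27–66% (ART) with ineffective matching. It is about 8–29% and 17–55% if pairs absorb half the variance, and about 6–11% and 8–25% if they absorb 90%. These figures rest on the protocol's expected counts, a single-period comparison and equal cluster sizes. The permutation floors and the missing cluster allowance do not depend on k.

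**What to change.** In Data analysis, make the primary analysis of each outcome a pre-specified comparison of the six cluster-level log rates, with starts assigned by residence and a t-based interval. State whether it is paired (2 df) or unpaired (4 df, conservative if matching works); either is defensible if fixed in advance. Then:
- keep Poisson or mixed models as secondary, with cluster effects and a small-sample correction;
- limit cluster-level adjustment to at most one covariate, such as the baseline rate, noting that it costs one df (leaving 3 unpaired or 1 paired);
- state that an exact randomisation test cannot go below p=0.25 (paired) or 0.10 (unpaired), so neither 5% nor 1% is reachable that way;
- state the assumed k and its source, and restate power under it.

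The cost is more than wording. At k=0.10 with ineffective matching, intervals on the log scale become about 1.245×2.776/1.960 = 1.8 times as wide for TB on 4 df and 1.245×4.303/1.960 = 2.7 times on 2 df. For ART the factors are 1.780×2.776/1.960 = 2.5 and 1.780×4.303/1.960 = 3.9. The stated 87.5% and 86.9% no longer apply. For k of 0.1 to 0.3 with ineffective matching, power is roughly 8–30% at alpha 5% and about 1.5–9% at the protocol's 1%.

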**SIGNIFICANCE OF EXPECTED FINDINGS**

# Policy relevance

This research will provide tools to (a) improve accessibility and quality of first-contact services for TB and HIV; (b) strengthen health systems through improved inter-provider interfaces; (c) focus on the most vulnerable groups in the poorest countries in the world; and (d) strengthen community participation and patient group interfaces with different providers.Malawi alongside Sudan have been chosen as linked field sites for conduct of the Triage-Plus research because these are poor countries within which the poor and vulnerable carry a heavy burden of communicable disease morbidity and mortality. Furthermore, because the Norwegian Heart and Lung patient organization (LHL) has pre-existing, strong links with two locally established NGO’s with a strong track record in implementation action research (REACH Trust in Malawi and Epi-Lab in Sudan).

**Poverty reduction through improved access to effective HIV and TB services.**

In the poorer countries in Sub-Saharan Africa (represented for this project by Malawi and Sudan), loss of income has a disproportionately severe impact on the health of the poor. The adverse economic impacts of TB and HIV are profound.

- TB sufferers are unable to work for an average of 3-4 months and lose around 20 per cent of annual household income as a result. Furthermore, the long and expensive treatment for TB can cost from 5 to 21% of annual household income. The macroeconomic implications are substantial, as 75 per cent of TB cases in developing countries occur among the economically active population (many of whom are women), and estimates suggest that the cost of TB-related productivity losses is significant.
- Terminal AIDS disease costs from 8 to 100% of household income. In Malawi HIV/AIDS combines with the food crisis to promote a vicious cycle: increased malnutrition weakens the resistance of people infected with HIV to opportunistic infections, thereby reducing the workforce available for agricultural and other work.
- The burden of these diseases among women is severe. Women play a vital role in wealth creation especially in the developing world and it has been argued that the ill health of women is one of the biggest obstacles to poverty reduction in the present day.

By improving access to effective services, Triage Plus has the potential to decrease wasteful consumption of resources through inappropriate or harmful therapy and decrease loss of earnings through ill health and so reduce household and macroeconomic poverty. This is in line with the Malawi Growth and Development Strategy (MDGS).

**ETHICAL CONSIDERATIONS**

**The project will follow established standards of ethical research involving patients. It will also aim to safeguard the rights of patients and others involved or affected by the research; transparency with appropriate forms of explanation to study participants;** Informed consent will be sought from all individuals participating in the project; **including young – study participants (even where consent will also be needed from guardians) (See appendix 5); maintaining the highest possible standards of research practices; which applies to research design, data collection, storage, analysis, interpretation and reporting guidelines.**

The project will involve the community in collecting sputum from chronic coughers in some instances. This will present as a challenge and risk for people that will be involved in the project. To reduce risk of infection of the participants, training will be organised for the informal healthcare providers and the package will include issues of safety during sputum collection. In addition, HSAs will be trained to support and supervise the informal healthcare providers’ activities.

Since the people involved in the project will be members of the community, the issue of confidentiality will be crucial. Training for community providers engaged by the project will include stipulations on confidentiality and regular checks that all providers continue to keep the status of the patients they identify and support confidential throughout the trial.

The issue of conducting a test and/or taking results of a test to patients may in some instances raise psychological harm to the patients being tested or getting the results. To decrease the psychological harm caused to the patients, the project will follow the NTP and NAC laid down guidelines when undertaking its project activities. In addition, the informal healthcare providers will be trained in counselling especially amongst those who will be involved in testing.

As an action research, there will be need to collect information of good quality so that the findings give comprehensive understanding of the project activities and findings. To ensure good quality information, the messages for health communication will be pilot tested and feedback will be incorporated in the manual and other training materials that will be developed. There will also be periodic follow-up interviews with members from informal healthcare providers, patients and members of the general community to check quality of information that is being disseminated in the project area.

*Potential benefits*

The community is expected to benefit from the intervention through development of their skills in delivery of services to their clients. There will also be attainment of new skill in areas of referral of TB suspects and HIV cases. New skills will also be gained in areas of disease recognition and care and support of TB and HIV infected people and well as AIDS patients. Members of the community that will be involved in the project will benefit by getting recognition from the community that they will be serving. Above everything else, the community will benefit from being linked up with the formal health service providers. The general community will benefit through awareness of advantages of accessing formal health systems medical services.

The project stands to benefit the patients that would be diagnosed during the project in the intervention area. Among others there will be increased access to good quality information and services. There will also be reduced costs to accessing TB and HIV related services as these services will be brought to the communities. There will also be increased support network within the community as various informal healthcare providers will be brought together to implement the project.

The benefit of the project will also extend to the formal health services providers. The health workers will relieved of work burden as some of the duties of HSAs such follow up of patients and contact tracing will be done by the volunteers from the different informal healthcare providers. The model will provide options for reaching targets for treatment ie TB cure rate, number of people starting on ART and treatment adherence for both TB and ART. Since both TB and HIV programmes are striving to integrate their activities at community level, the model will provide an opportunity of integrating the TB and HIV programmes at community level.
